#### Data handling and record keeping

Study data is recorded by remote data entry into a web-based electronic case report form (eCRF) developed for the study by the Robertson Centre, Glasgow. eCRF data is anonymous and will identify study participants by their assigned study numbers only. All missing data, possible duplication and data outside preset limits for each parameter is queried by the Management Centre, and will be internally validated before database lock.

### Statistical analysis plan

The study has a hierarchical coprimary end point which will be the difference in the home systolic BP between spironolactone and placebo, followed by the difference in home systolic BP between spironolactone and the average of the other two active drugs, (doxazosin and bisoprolol), followed by the difference in home systolic BP between spironolactone and each of the other two active drugs. For secondary analyses, similar analyses of the primary analysis will be made using clinic blood pressure. We will also compare the proportion of patients achieving target blood pressure (home and/or clinic) with each of the three active treatments. We will examine the proportion of patients controlled by each drug who are also controlled by the run-out treatment, amiloride. We will look at the direction of correlation between plasma renin and the blood pressure response to each drug. We will then describe differences between blood pressure response to each drug at extremes of plasma renin. Similar analyses will be performed for each haemodynamic variable. We will also examine the predictive value of the baseline measurements of cardiac output, systemic vascular resistance and thoracic impedance. The study will also explore the cost-benefit of using plasma renin to stratify best treatment in individual patients. An additional end point will be analyses of relationships between genetic factors and pharmacodynamic responses.

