#### Run-out phase of the study

To evaluate if amiloride would be a suitable alternative to spironolactone, the run-out phase of the study was used to evaluate the BP-lowering effectiveness of amiloride using an open label design. Patients were eligible for the amiloride open label run-out phase of the study as long as they did not develop potassium levels ≥5.5 mmol/L during the study treatment cycles. If eligible, patients were prescribed open-label amiloride 10 mg once daily for 6 weeks, followed by forced titration to amiloride 20 mg once daily for a further 6 weeks. Patients were evaluated at study sites at 6 and 12 weeks, and BP recorded in accordance with procedures for the main study. In the remaining patients, physicians will choose the exit drug based where possible on pretrial experience of fourth and fifth-line treatment. For patients with uncontrolled BP at the end of the treatment cycles, or the amiloride run-out phase, it was considered unethical to wait for completion of the overall study before their best treatment option could be revealed. Thus, at the end of the main study, the data base will be locked for individual patients and the data centre can reveal the best treatment option for an individual patient at the request of the study site PI. The full schedule of assessment and procedures is shown in the table 1.

**Table 1 BMJOPEN2015008951TB1:** PATHWAY 2 Study schedule and procedures

	Screening	Randomisation	Phase 1		Phase 2		Phase 3		Phase 4	
	Week −4	Week 0	Week 6	Week 12	Week 18	Week 24	Week 30	Week 36	Week 42	Week 48
Informed consent	X									
Medical history	X	X								X
Clinical examination	X									X
Concomitant medications	X	X	X	X	X	X	X	X	X	X
Weight	X	X	X	X	X	X	X	X	X	X
Inclusion/exclusion criteria check	X	X								
Clinic BP and heart rate	X	X	X	X	X	X	X	X	X	X
Home BP and heart rate*		X	X	X	X	X	X	X	X	X
Home BP 6 h after witnessed administration of A+C+D medication†		X								
12 lead ECG	X									X
PEFR	X	X	X	X	X	X	X	X	X	X
Blood tests—electrolytes, urea, creatinine	X	X	X	X	X	X	X	X	X	X
Blood tests—glucose, lipids, uric acid, Ca++	X									X
Blood tests—cholesterol, HDL and triglycerides		X								X
Blood tests –plasma renin/aldosterone‡		X								
Pharmacogenetics§		X								
Blood tests—haematology, albumin, glucose	X			X		X		X		X
Blood—serum ace levels		X								
24 h urinary electrolytes		X								
Urinalysis	X	X		X		X		X		X
HCG testing pregnancy	X	X		X		X		X		

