#### Sample size calculation

The sample size was based on detecting a difference of 3 mm Hg (SD=12 mm Hg) in systolic blood pressure between each of the experimental drugs and the placebo treatment with 90% power, and using a single sample t test at the 0.003 significance level (0.01 level adjusted for 3 comparisons being made). Variances in these calculations were estimated from the within-subject (interdrug) variability observed in 90 patients participating in the Cambridge crossover studies of the major drug classes.

The estimated requirement was for 294 patients; so we set a recruitment target of 346 to allowing for a dropout rate of 15%. This number also provides similar power to detect a twofold increase in superiority through renin profiling, namely a 6 mm Hg difference in systolic BP between best and second-best drug within each quartile of plasma renin.

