A patient will be deemed a “responder’ if they meet any of these two conditions; (1) HBPM systolic BP (SBP) <135 mm Hg; (2) HBPM SBP has fallen ≥10 mm Hg since baseline. Responder rates will be analysed by logistic regression and will be adjusted for baseline covariates. Withdrawal rates will be analysed by logistic regression and will be adjusted for baseline covariates.

The main secondary objective is to use plasma renin measurements to evaluate an ‘α, β, Δ’ rule for the selection of the fourth-line drug for patients with drug-resistant hypertension (see secondary objectives above). The hypothesis is that plasma renin (measured on a background of 3 drugs, ie, A+C+D), will predict the most effective fourth-line drug. We shall identify the best treatment for each patient, that is, the one on which they achieved the lowest BP. This is a categorical response and we shall use a logistic model to estimate the probability of each treatment being declared the best as a function of baseline renin. Superimposed plots of these probabilities (see figure 2) will show the range of renin values for which each treatment is most likely to be the best choice. We will also, in the same way, evaluate haemodynamic parameters indicative of sodium retention and volume status, that is, cardiac output, peripheral resistance and bioimpedance as predictors of the best fourth-line treatment among the three active treatments. An additional end point will be analyses of relationships between genetic factors and pharmacodynamic responses.

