### Evaluating further diuretic therapy

Since spironolactone has been associated with the development of gynaecomastia, estimated to occur in approximately 6% of patients,^9^ we also incorporated an open label run-out phase for the study during which patients will be treated with amiloride, a potassium-sparing diuretic, to determine if this replicates the effects of spironolactone on BP, thus providing an alternative further diuretic therapy for those intolerant of spironolactone.

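### The one amiloride analysis the article names, concordance of BP control, does not measure whether amiloride replicates spironolactone's effect on blood pressure

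*Protocol article*

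**What the plan says.** The article gives the purpose of the run-out twice. Under Run-out phase of the study the aim is "To evaluate if amiloride would be a suitable alternative to spironolactone", and the same sentence says "the run-out phase of the study was used to evaluate the BP-lowering effectiveness of amiloride using an open label design". The discussion section Evaluating further diuretic therapy says that amiloride is given "to determine if this replicates the effects of spironolactone on BP".

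The Statistical analysis plan section names one analysis for it: "We will examine the proportion of patients controlled by each drug who are also controlled by the run-out treatment, amiloride". The sentence before it reads "We will also compare the proportion of patients achieving target blood pressure (home and/or clinic) with each of the three active treatments". The primary and secondary lists under Statistical model contain no amiloride comparison. No ranking, test, margin or decision rule is attached to the proportion.

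Control is not given a number for this purpose. The nearest cut-off is the first responder condition, "HBPM systolic BP (SBP) <135 mm Hg". Patients enter the run-out "as long as they did not develop potassium levels ≥5.5 mmol/L during the study treatment cycles", and BP is measured there by the main-study procedures.

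**The concern.** The aim is a comparison of two drugs' effects on BP. The named statistic is a conditional proportion: among patients below a cut-off on drug X, the share also below it on amiloride. Two things other than similarity move it.

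- **Ease of control.** A weaker drug brings only the easier patients below the cut-off, and these are more likely to be controlled on anything. If spironolactone is the strongest drug, as the primary objective expects, its controlled group contains harder patients and its share is pushed down.
- **Repeatability.** A patient controlled on one variable reading may not be controlled on the next, even on the same drug. How often depends on how much of the within-patient variation is stable response to that drug.

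The run-out is meant to support amiloride for patients who cannot take spironolactone. A share that could come equally from an equivalent or a weaker drug does not settle that.

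**Working it through.** **1. The plan's own figure.** Inputs from Sample size calculation: "detecting a difference of 3 mm Hg (SD=12 mm Hg) in systolic blood pressure", 90% power, single-sample t test at 0.003. With noncentrality 3√n/12 and a two-sided test, n = 294 gives 90.1% power and n = 293 falls just short of 90%. Then 294/0.85 = 345.9, so 346. Both figures reproduce. SD 12 therefore acts as the SD of a within-patient difference, and the variance per treatment period is 12²/2 = 72 (SD 8.5).

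**2. Model.** Home SBP = drug mean + patient level (SD s) + patient-by-drug response + residual. The last two terms have total variance 72, and ρ is the fraction of it that is repeatable drug-specific response. A true copy of spironolactone has the same mean and the same patient-by-drug response, with a fresh residual. Then:

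- correlation of amiloride with spironolactone = (s² + 72ρ)/(s² + 72)
- correlation of amiloride with any other treatment = s²/(s² + 72)
- share = Φ₂(z_X, z_A; r)/Φ(z_X), with z = (135 − mean)/√(s² + 72)

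Assumptions, not document figures: control means below 135 mm Hg; placebo mean 142; s = 8; other actives 3 and spironolactone 6 mm Hg below placebo. Total SD is √136 = 11.7. Controlled: 46.6% on spironolactone, 36.6% on another active, 27.4% on placebo.

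**3. Share re-controlled by an exact copy of spironolactone.**

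| ρ | given spironolactone | given another active | given placebo |
|---|---|---|---|
| 0 | 63.2% | 66.7% | 70.2% |
| 0.1 | 65.3% | 66.7% | 70.2% |
| 0.2 | 67.5% | 66.7% | 70.2% |
| 0.5 | 74.7% | 66.7% | 70.2% |
| 1 | 100% | 66.7% | 70.2% |

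The placebo column matters only if placebo counts as one of the drugs in the planned statistic, which the article does not say.

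**4. How far the reversal reaches.** The scan covered placebo means 140 to 148, s from 6 to 15, other actives 3 to 4 and spironolactone 6 to 9 mm Hg below placebo. The spironolactone share stops being below the other actives' once ρ passes 0.09 to 0.54, depending on the scenario. It passes the placebo share once ρ exceeds 0.19 to 0.71. If spironolactone is no better than the other actives, the shares tie at ρ = 0 and spironolactone is higher for any larger ρ.

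**5. Same share, different drug.** In the step 2 scenario, let amiloride be 3 mm Hg weaker than spironolactone (mean 139 against 136) with ρ = 0.5. The correlation is (64 + 36)/136 = 0.735 and the share is 63.0%. The exact copy at ρ = 0 gives 63.2%. The 3 mm Hg gap is the difference the trial was sized to detect.

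**6. The direct comparison.** The expected paired difference is 0 for the copy and 3 mm Hg for the weaker drug, whatever ρ is. The 95% half-width is t × 12/√n:

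- n = 294: 1.968 × 12/17.15 = 1.4 mm Hg
- n = 250: 1.970 × 12/15.81 = 1.5 mm Hg
- n = 200: 1.972 × 12/14.14 = 1.7 mm Hg

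The article does not give the number entering the run-out, so these values of n are assumed.

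**The case against.** Several counter-arguments have force.

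- **Conditional reversal.** A reader might infer that the statistic would always rank a copy of spironolactone as least like it. The documents do not support that. It requires ρ to be small, and the article's own heterogeneity and renin hypotheses presuppose some individual drug-specific response. The SD of 12 is described as inter-drug variability, so it may contain such response. A literal copy scores 100%.
- **Small reversal.** At ρ = 0 the gap to the other actives is 66.7 − 63.2 = 3.5 points. With an assumed 250 entrants, about 0.466 × 250 = 116 are spironolactone-controlled, and the share's own 95% half-width is 1.96 × √(0.632 × 0.368/116) = 8.8 points.
- **Separation within a scenario.** A reader might also infer that the share can never tell an equivalent drug from a weaker one. That goes too far. At fixed means, SDs and ρ a weaker drug does score lower. Overlap appears when scenarios are pooled, and the trial will observe its means and SDs.
- **No decision rule.** The article only undertakes to examine the proportion. It ranks nothing and rules out no other analysis, and evaluating BP lowering suggests that a BP comparison is contemplated.
- **Same patients.** The proportion needs an amiloride reading, so it is already confined to run-out entrants.

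All of this narrows the point. It does not remove the mismatch, because ρ is not given and reading the share as similarity requires it. Nor is this only a complaint about detail left to a fuller document: the article states a specific statistic, and that statistic does not answer the question the article poses.

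**Conclusion.** The point holds in a limited form. The only named amiloride analysis mixes similarity to spironolactone with ease of control and with an unstated degree of repeatability, so it does not measure the run-out's stated aim. In the worked scenario an exact copy and a drug 3 mm Hg weaker both give about 63% under different repeatable shares. Where spironolactone is superior and the repeatable share is below roughly 0.1 to 0.5, a true copy can appear less concordant with spironolactone than with the weaker actives. These sizes rest on assumed baseline means, between-patient SDs, drug effects and a 135 mm Hg control threshold; only the SD of 12 comes from the article. The primary comparisons of the randomised treatments are not affected.

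**What to change.** Make the main run-out analysis the within-patient difference in home systolic BP, amiloride minus spironolactone and amiloride minus placebo. Use readings on the maximum tolerated dose of each, as the primary analysis does, among patients who entered the run-out. Report each difference with a 95% CI and use the main mixed model's covariates. Keep the concordance proportion as description only. State beside the estimate that amiloride always comes last, is given open label, and is given only to patients selected on potassium, and that none of these is controlled.

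The cost is a change of wording and one extra model on data already collected. The estimate remains subject to the three stated limits, so it would support a qualified statement about amiloride and not a randomised comparison.

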#### Secondary objectives

The main secondary objective is test the use of plasma renin measurement to evaluate the ‘α, β, Δ’ rule^8^ for the selection of the fourth-line drug for patients with drug resistant hypertension—where α represents α-blockade, β represents β-blockade and **Δ** represents ‘further diuretic therapy’. We propose that α-blockade will be the most effective fouth-line treatment at lowering BP in patients in the mid-tertile of plasma renin (expected to be ≥20 mU/L but <100 mU/L); β-blockade will be the most effective drug when the renin level in in the top tertile (expected to be ≥100 mU/L) as this drug inhibits renin secretion; further diuretic therapy with spironolactone will be the most effective drug in the lowest tertile of plasma renin (<20 mU/L), indicative of renin suppression due to excessive sodium retention. Further secondary analyses will use physiological phenotyping of non-invasive haemodynamic parameters indicative of sodium retention and volume status, that is, cardiac output, peripheral vascular resistance, bio-impedance, pulse wave analysis and pulse wave velocity to evaluate mechanisms for resistant hypertension and determine if these methods can help better stratify the best treatment for individual patients with resistant hypertension.

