### Evaluating strategies for treatment stratification

The PATHWAY 2 study also incorporates measurement of plasma renin and a detailed physiological evaluation of patients with resistant hypertension (eg, cardiac output, systemic vascular resistance, arterial stiffness and thoracic bioimpedance) to determine if these tests can better predict the best response to a specific drug type. The principal secondary hypothesis tests an ‘α, β, Δ’ rule^8^ which states that (1) further diuretic therapy (Δ), that is, spironolactone, will be the best therapy in patients with evidence of sodium and volume overload, and this will be predicted by a low plasma renin at baseline, despite treatment with A+C+D; (2) that a β-blocker (β), that is, bisoprolol, which suppresses renin would be the best treatment in patients with a high plasma renin at baseline; and (3) that an α-blocker (α), that is, doxazosin, would be the best treatment in those with a plasma renin level in the mid-tertile. Such a finding would suggest potential utility in measuring plasma renin to stratify the most appropriate treatment for individual patients. This concept was suggested many years ago^24^ and previous studies have suggested that physiological phenotyping of sodium/volume status (for which plasma renin is a surrogate) have suggested that this can predict the most effective treatment.^25^ In this regard, our primary hypothesis states that we expect the most common underlying pathophysiology for resistant hypertension will be sodium/volume overload, resulting in a low plasma renin at baseline, and consequently the best response will be obtained with further diuretic therapy, that is, spironolactone, in most patients.

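### The named analyses of BP response against renin cannot show the predicted mid-tertile α-blocker advantage, and none estimates the within-stratum BP difference for which power is stated

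*Protocol article*

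**What the plan says.** **The hypothesis.** Secondary objectives states the middle part of the α, β, Δ rule as follows: "We propose that α-blockade will be the most effective fouth-line treatment at lowering BP in patients in the mid-tertile of plasma renin". The expected bands are below 20, 20 to below 100, and 100 mU/L or above. The Introduction makes the same prediction, and the Discussion (Evaluating strategies for treatment stratification) repeats that the α-blocker "would be the best treatment in those with a plasma renin level in the mid-tertile".

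**BP response against renin.** The opening paragraph of the Statistical analysis plan names two analyses. The first is: "We will look at the direction of correlation between plasma renin and the blood pressure response to each drug". The second is: "We will then describe differences between blood pressure response to each drug at extremes of plasma renin".

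**Best drug against renin.** Statistical model adds a third analysis, tied explicitly to the rule. Each patient's best drug is "the one on which they achieved the lowest BP", and "we shall use a logistic model to estimate the probability of each treatment being declared the best as a function of baseline renin". Plots of these probabilities "will show the range of renin values for which each treatment is most likely to be the best choice".

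**Power.** The Abstract and the Sample size calculation both state power for a 6 mm Hg systolic difference between best and second-best drug by renin stratum. The Abstract uses tertiles; the Sample size calculation uses quartiles.

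**The concern.** The rule predicts a pattern that is not monotone for doxazosin: an advantage in the middle third and none in the outer thirds. A direction of correlation summarises a monotone trend. A comparison at the extremes leaves out the middle by construction. The two named BP-response analyses can therefore support the spironolactone and bisoprolol parts but cannot show the doxazosin advantage, even if it is real and large.

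The best-drug model fills part of the gap, but it answers in probabilities. A clinician deciding whether to measure renin needs to know how many mm Hg the choice is worth, and the power statement is expressed in that unit. As written, readers would have BP differences for the ends of the renin range, a trend direction that carries no information on the α-blocker part, and a set of probability curves. They would have no mm Hg estimate for the middle third.

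**Working it through.** **Inputs.** From Sample size calculation: difference 3 mm Hg, SD 12 mm Hg, 90% power, one-sample t test at 0.003, 294 evaluable patients, 346 recruited with 15% dropout, and a 6 mm Hg difference by renin stratum. From Secondary objectives: tertile boundaries expected at 20 and 100 mU/L.

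**1. Reproduce the plan's figure.** For a one-sample t test the noncentrality is δ√n/SD. With δ = 3, n = 294 and SD = 12 it is 3 × √294/12 = 4.29. At two-sided 0.003 this gives 90.1% power, and 294 is the smallest n that reaches 90%. Dropout: 294/0.85 = 346. Both figures reproduce.

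**2. What the renin power statement implies.** Doubling the difference and quartering the sample leaves the noncentrality unchanged: 6 × √(294/4)/12 = 4.29. The claim of similar power therefore corresponds to a BP contrast between two drugs inside one quarter of the patients. None of the three named renin analyses estimates such a contrast over all strata.

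**3. What a correlation shows if the rule is true.** Score the renin thirds −1, 0, +1 and give each drug a 6 mm Hg advantage in its own third. The covariance of response with the score is then:

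- spironolactone: (−1×6 + 0×0 + 1×0)/3 = −2
- doxazosin: (−1×0 + 0×6 + 1×0)/3 = 0
- bisoprolol: (−1×0 + 0×0 + 1×6)/3 = +2

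The doxazosin direction is undetermined. In 400 simulated trials under this scenario (294 patients, between-drug SD 12, lognormal renin with tertiles at 20 and 100 mU/L), the rank correlation averaged 0.00 and was positive in 50%.

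**4. What the best-drug model shows.** With a true 6 mm Hg advantage over both other active drugs and a between-drug SD of 12, a drug is labelled best in about 55% of patients, against 33% by chance. The label drops the size of the difference. In the same scenario, a multinomial logistic model linear in log renin put doxazosin on top at median renin in 53% of trials when the middle part of the rule was true and in 1% when it was false. Doxazosin was on top at some renin value in about 70% of trials. The linear form is an assumption; the article states none.

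**5. What a tertile contrast would deliver.** Evaluable patients per tertile: 294/3 = 98. Assume that SD 12 also applies within a tertile and that the two drugs are named in advance.

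| Contrast | Noncentrality | Power at 0.003 | Power at 0.05 |
|---|---|---|---|
| 6 mm Hg, tertile (n = 98) | 6√98/12 = 4.95 | 97% | 99.8% |
| 3 mm Hg, tertile (n = 98) | 3√98/12 = 2.47 | 29% | 69% |
| 6 mm Hg, quartile (n = 73) | 6√73/12 = 4.27 | 88% | 99% |

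The middle part of the rule needs doxazosin to beat both other active drugs. In simulation both mid-tertile paired contrasts reached 0.05 in about 99% of trials when the true advantage was 6 mm Hg. This is not a like-for-like comparison with the 53% in step 4, because being the top curve is not a test at 0.05. It shows only that the data support a BP contrast in the middle third.

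**The case against.** The strongest reply is that the named analysis for the main secondary objective is the best-drug model, not the two looks in the opening paragraph. That model runs over the whole range of baseline renin, its outcome comes from BP, and the rule itself is worded as which drug is best in each band. This stands. A reader might infer from the opening paragraph alone that only two parts of the rule are examined, or that doxazosin is bound to appear never best. The documents do not support that: in step 4 the model separates a true from a false middle part (53% against 1%), even with a linear term.

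The extremes analysis is not wholly silent either. A doxazosin win at either end would contradict the rule. It is the mid-tertile advantage itself that the analysis cannot show.

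It is also fair to say that the article condenses a fuller plan, that link, scale and curvature are commonly left to that plan, and that no formal test is named for any single part of the rule, so the lack of one is not special to the middle. For that reason the unstated model form is not held against the article. What remains is a choice the article does make: it restricts the BP comparison to the extremes of renin, although its hypothesis concerns the middle as well and its power statement concerns BP differences by stratum.

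Finally, the 0.05 level is not one the protocol states, and at its own 0.003 a 3 mm Hg mid-tertile difference would usually be missed. That limits what the added contrast can promise but does not argue against reporting it with a confidence interval.

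**Conclusion.** The point holds in a limited form. The two named BP-response analyses cannot show a mid-tertile α-blocker advantage. The best-drug model does examine it, but without a mm Hg estimate and, under a plain linear term, with only moderate sensitivity. No named analysis estimates the 6 mm Hg best versus second-best difference by renin stratum on which the secondary power statement rests.

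A single 6 mm Hg contrast in the middle third has about 97% power at two-sided 0.003; a 3 mm Hg contrast has about 29%. These figures assume 98 evaluable patients per tertile, SD 12 mm Hg within tertiles and two drugs named in advance; requiring doxazosin to beat both comparators gives somewhat less. The simulation figures assume lognormal renin, a rule that is exactly true, and a linear log-renin model. The matter concerns a secondary objective and leaves the primary analysis untouched. It is worth correcting because the improvement is nearly free.

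**What to change.** - In the opening paragraph of the Statistical analysis plan, change the second renin analysis so that drug differences in BP response are described within each tertile of plasma renin, not only at the extremes.
- Take these from the mixed model already planned under Statistical model by adding renin tertile and its interaction with treatment. Report the contrasts with confidence intervals for all three parts of the rule, including doxazosin minus spironolactone and doxazosin minus bisoprolol in the middle tertile. For a simple paired contrast with 98 patients the 95% half-width would be about 1.985 × 12/√98 = 2.4 mm Hg.
- Allow curvature wherever renin enters as a continuous term, including the best-drug model (for example, a quadratic in log renin).
- State that the direction of correlation is not evidence for or against the α-blocker part.
- Use tertiles in the Sample size calculation, to match the rule and the Abstract.

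The cost is some wording and one extra set of contrasts. No new data, visits or patients are needed.
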